#### Study design

2.5.1

This protocol paper, developed using the intervention mapping (IM) framework, describes the planning of a 12-week cluster-randomized mixed-methods pilot study, incorporating both quantitative and qualitative data collection and analysis. The target population included first-year upper secondary school students from a broad region in southeastern Norway (three counties), aiming for balanced representation of academic and vocational programs. Invitations were sent to 27 upper secondary schools, and five agreed to participate (three academic, two vocational). One vocational school, twice the size of the others, contributed approximately 200 students, while each of the remaining four contributed about 100 students. Of 739 eligible students, 519 provided consent. The inclusion criteria for participation were students aged 16–17 years, with exclusion criteria defined as disabilities preventing participation and/or illnesses posing health risks.

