#### Randomization procedure

2.5.2

The MOVE12-pilot study was designed as a two-arm, three-level cluster randomized controlled trial (RCT), featuring an intervention group (IG) and a control group (CG), with participants organized within classrooms and schools. Participants were randomly assigned to either the IG or the CG (1:1) by the principal investigator (PI). At the three academic schools (class size: 25–30), four relatively homogeneous classes were identified, and randomization involved drawing from two boxes (one for group assignment, one for classes) in alternating turns until all classes were assigned. At the two vocational schools (class size: 12–17), classes were stratified by gender, size, and subject area before following the same procedure using four boxes (A–D). Twice as many groups were drawn from the vocational school that was double the size of the others.

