### Quantitative and qualitative data analysis

2.7

Data analysis will combine quantitative and qualitative approaches. To examine between-group differences in continuous outcome measures from baseline to the 12-week follow-up, a linear mixed model (LMM) will be applied. LMM addresses the nested data structure of MOVE12 (students within classrooms, classrooms within schools) by incorporating random intercepts to account for intra-class correlation and hierarchical clustering effects (71). Additionally, LMMs handle missing data robustly under the assumption of missing at random (72), a common scenario in school-based interventions. Within-group changes will be assessed using dependent *t*-tests, and potential associations between ordinal outcome measures will be explored through multiple and binary regression analyses. All statistical analyses will be conducted using STATA version 18.0 (73).

Qualitative methods will be used to identify key themes from the planned focus group interviews, guided by determinants such as knowledge, attitude, self-efficacy, basic psychological needs (autonomy, competence, relatedness), social support, school culture, and the physical environment. This qualitative approach aims to deepen our understanding of how these factors influence participants' experiences and engagement with the intervention, thereby informing both practical implementation and theoretical implications. Qualitative data will be analyzed thematically using NVivo 14 software to support and manage the analytic process (74).

*a priori* sample size calculations with G-Power (75) suggested that a sample of 580 participants would be sufficient to detect a moderate effect size (*d* = 0.3), assuming a two-group design, 80% power, and an alpha of.05.

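### The stated inputs give 352 students, not 580, and the calculation states no allowance for the randomisation of whole classes, so 80% power for d = 0.3 is not established for the 519 enrolled

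*Protocol article*

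**What the plan says.** All references are to the protocol article.

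- **Quantitative and qualitative data analysis (2.7), sample size.** The G-Power calculation "suggested that a sample of 580 participants would be sufficient to detect a moderate effect size", with d = 0.3, "assuming a two-group design, 80% power, and an alpha of.05". These are all the inputs given. Sidedness, the outcome, clustering and dropout are not mentioned.
- **Randomization procedure (2.5.2).** The trial is a "two-arm, three-level cluster randomized controlled trial (RCT"). Classes were drawn within schools. The three academic schools had four classes each, of 25–30 students. The two vocational schools had classes of 12–17, and their number is not stated. Allocation was 1:1.
- **Study design (2.5.1).** "Of 739 eligible students, 519 provided consent". That is 61 below 580, and power is not restated for it.
- **Section 2.7, analysis.** Between-group differences from baseline to 12 weeks are to be estimated by a linear mixed model with random intercepts for the nesting of students in classes and classes in schools.

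**The concern.** The sentence raises two problems.

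The first is internal and needs no outside assumption: N and the stated power do not belong together under the inputs listed.

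The second concerns design. The analysis recognises correlation within classes, but the stated calculation does not. Students in a class share a timetable, teachers and classmates who lead the breaks, and one outcome is the learning environment of the class itself. Positive within-class correlation is therefore to be expected for at least some outcomes, and it reduces the information in a given number of students.

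At stake is how null results will be read. A non-significant difference in fitness, activity or wellbeing would be taken as coming from a trial with at least 80% power for d = 0.3. A main intervention is planned to follow (2.3.2), so that reading could carry forward.

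**Working it through.** **Step 1. Reproduce the stated figure.** Inputs from 2.7: two equal groups, d = 0.3, alpha 0.05 (taken as two-sided), power 80%.

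Normal approximation: N = 4(1.960 + 0.842)² / 0.3² = 348.8, or 350 with equal arms. The exact two-sample t test gives the following.

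| Total N | Power for d = 0.3, independent students |
|---|---|
| 352 | 80.1% |
| 402 | 85% |
| 470 | 90% |
| 519 | 92.7% |
| 580 | 95.0% |

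A one-sided test at 80% power needs 278. The stated inputs therefore do not reproduce 580, whereas a two-sided test at 95% power gives it exactly. Two other routes to 580 are arithmetically possible:

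- a design effect of 580/352 = 1.65;
- dropout inflation of about 39% (352/0.607 = 580).

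The article states neither.

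**Step 2. Set up the class-randomised calculation.** The article gives no ICC and no total number of classes, so these are assumptions:

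- 12 academic classes (3 schools × 4) with about 22 consenting students each, and about 21 vocational classes with about 12 each: 33 classes, coefficient of variation (CV) of class size 0.31;
- ICC 0.02, 0.05 and 0.10;
- d = 0.3, two-sided alpha 0.05, t test with 33 − 2 = 31 degrees of freedom.

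Formulas, with m the mean class size and ρ the ICC:

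- design effect DE = 1 + [(1 + CV²)m − 1]ρ
- effective N = N/DE
- non-centrality = 0.3·√(effective N/4)

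For N = 519: m = 519/33 = 15.7, and DE = 1 + (1.096 × 15.7 − 1)ρ = 1 + 16.2ρ.

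**Step 3. Power without baseline adjustment or attrition.**

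| ICC | DE at 519 | Effective N at 519 | Power at 519 | Detectable d at 519 (80%) | Power at 580 |
|---|---|---|---|---|---|
| 0.02 | 1.32 | 392 | 82% | 0.29 | 85% |
| 0.05 | 1.81 | 286 | 69% | 0.34 | 72% |
| 0.10 | 2.62 | 198 | 53% | 0.41 | 55% |

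Power falls to 80% at an ICC of about 0.025 for 519 students and about 0.03 for 580. A separate check used 28–36 classes, unequal sizes and a normal approximation. At 519 it gave 83–85%, 70–74% and 54–60% for the same ICCs. Using a t distribution on (classes − 2) degrees of freedom lowers those figures by about 1–4 points.

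**Step 4. Two factors that move the answer in opposite directions (519 enrolled).** Attrition reduces N. Baseline adjustment divides the outcome variance by 1/(1 − r²), so the non-centrality is divided by √(1 − r²), where r is an assumed correlation between baseline and follow-up.

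| ICC | 10% to 20% attrition, unadjusted | r = 0.5, no attrition | r = 0.7, no attrition |
|---|---|---|---|
| 0.02 | 79% to 75% | 91% | 98% |
| 0.05 | 67% to 64% | 81% | 93% |
| 0.10 | 52% to 50% | 66% | 82% |

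**The case against.** The strongest case for the plan has four parts.

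**The trial may have the power it claims.** Because 580 exceeds 352, there is slack: 580 tolerates a design effect of 1.65 and 519 tolerates 519/352 = 1.47 (before the small-sample loss of degrees of freedom). At ICC 0.02 or below, 519 students exceed 80% power before attrition. The planned comparison runs from baseline to follow-up, so an unadjusted calculation is pessimistic for most outcomes, and drawing classes within schools may help further. This stands. A reader might infer from the missing ICC that the trial is underpowered for d = 0.3. The document does not support that: it gives no ICC, baseline correlation or attrition rate.

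**The calculation may have allowed for clustering without saying so.** A one-sentence summary could hide a design effect of about 1.65. This cannot be excluded, so it is an inference that the authors treated students as independent. The inference is a likely one, since 580 matches the independent-samples t test at 95% power exactly and nothing in the text points to inflation.

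**The analysis already handles clustering.** The mixed model has random intercepts for classes and schools. This stands, and it means the concern is with the power statement and not with the validity of the planned between-group model.

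**This is a pilot.** Its primary outcomes are adherence, feasibility and experience, explored through focus groups (2.6.1), and a two-group d does not apply to those. The shortfall from 580 to 519 is disclosed, and 519 still exceeds 352. This lowers the severity. It does not rescue the sentence, which makes a claim of sufficiency without naming the outcome it concerns.

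**Conclusion.** The sample-size sentence is wrong or incomplete as published. Without any outside assumption, the stated inputs give 352 and not 580; 580 corresponds to 95% power for independent students. Also on the face of the article, no clustering quantity enters the stated calculation although classes were randomised.

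What remains conditional is the power actually achieved. Over the assumed ICCs of 0.02–0.10, power at 519 runs from 82% down to 53% unadjusted, lower with attrition and higher with baseline adjustment. These figures rest on 33 assumed classes with a size CV of 0.31, and on assumed ICCs, correlations and attrition rates. The supportable conclusion is that 80% power for d = 0.3 has not been shown, not that it is absent.

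Severity: moderate.

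**What to change.** Replace the sample-size sentence in 2.7 with a short paragraph that:

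1. resolves the mismatch between 580 and 80% power, saying whether 95% power was entered or some inflation was applied, and by how much;
2. calculates for the class-randomised design, stating the number of classes, the mean and CV of class size, and ranges for the ICC (for example 0.02, 0.05 and 0.10), the baseline correlation and attrition;
3. gives power for d = 0.3, or the minimum detectable effect, for the 519 students enrolled;
4. names the secondary outcome to which the figure applies;
5. drops the unqualified claim that the sample is sufficient.

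The cost is one paragraph and a stated power that may look less favourable. No extra students, and no change to the design or the mixed model, are needed.

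### The sample size of 580 matches 95% power, not the stated 80%: the stated inputs give 352

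*Protocol article*

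**What the plan says.** The last paragraph of section 2.7 (Quantitative and qualitative data analysis) is the only sample-size justification in the article. It says that "sample size calculations with G-Power (75) suggested" that "a sample of 580 participants would be sufficient to detect a moderate effect size", with d = 0.3, "assuming a two-group design, 80% power, and an alpha of.05". It does not say whether the test is one- or two-sided. It mentions no ICC, design effect, dropout allowance or multiplicity adjustment.

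Section 2.5.2 (Randomization procedure) gives 1:1 allocation and describes a "two-arm, three-level cluster randomized controlled trial (RCT"), with whole classes drawn to the arms. Class sizes are 25–30 at the academic schools and 12–17 at the vocational schools. Section 2.5.1 (Study design) reports that 519 of 739 eligible students consented.

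**The concern.** Apart from sidedness, the sentence gives every input that a two-group t-test calculation needs, so the figure can be checked directly. For a standardised difference of 0.3 at 80% power, 580 is far too large to be a rounding difference or the result of a different approximation.

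Two things are at stake. First, a reader who sets the 519 consenting students against 580 would conclude that the trial missed an 80% target, which the listed inputs do not support. Second, the reader cannot tell whether 580 precedes any allowance for clustering or already contains one. That affects how null results on the secondary outcomes are read. It also affects planning of the main intervention that section 2.3.2 says will follow, if the figure is carried forward.

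**Working it through.** **Inputs.** d = 0.3, alpha = 0.05 and power = 80%, with two groups (section 2.7); 1:1 allocation (section 2.5.2). Sidedness is not stated, so both were tried.

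**Formula.** For n per arm, the t statistic has 2n − 2 degrees of freedom and noncentrality d·√(n/2). The required n is the smallest integer at which power reaches its target. As a rough check, the normal approximation to the total is 4·(z₁₋α/₂ + z_power)²/d².

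**Attempt to reproduce 580 from the stated inputs**

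- Normal approximation, two-sided, 80%: 4·(1.960 + 0.842)²/0.09 ≈ 349, or 350 after rounding up to equal arms.
- Exact, two-sided, 80%: n = 175 gives 0.799 and n = 176 gives 0.801, so 176 per arm, **352** in total.
- Exact, one-sided, 80%: 139 per arm, **278** in total.

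Neither gives 580.

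**Which setting does give 580?** Exact totals at d = 0.3 and alpha 0.05:

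| Power | Two-sided | One-sided |
|---|---|---|
| 80% | 352 | 278 |
| 85% | 402 | 322 |
| 90% | 470 | 382 |
| 95% | **580** | 484 |

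Only two-sided 95% power gives 580. The match is exact: 289 per arm gives 0.9495, just short, and 290 gives 0.9502.

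**Size of the mismatch**

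- 580/352 = 1.648, so the stated total is 65% above what its inputs need.
- Power at 290 per arm for d = 0.3 is 95.0%, 15 points above the stated value.
- With 580 and 80% power, the detectable difference is d = 0.233.

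**Could an unstated adjustment explain it?**

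- *Dropout alone:* 1 − 352/580 = 39%.
- *Clustering alone:* a design effect 1 + (m − 1)·ICC = 1.648 needs ICC = 0.648/(m − 1). This is 0.059 at m = 12, 0.043 at m = 16, 0.040 at m = 17, 0.027 at m = 25 and 0.022 at m = 30.
- *Smaller alpha, 80% power, two-sided:* alpha 0.01 gives 524 and 0.005 gives 596, so neither gives 580.

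The ICC values are not implausible, but the article mentions no such adjustment.

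**The 519 who consented.** Ignoring clustering, arms of 260 and 259 give 92.7% power at d = 0.3. That figure only shows what the stated inputs imply; it does not describe this trial, because classes were randomised. As an illustration, assume 16 students per class, no school-level term, and an effective size of 519/[1 + 15·ICC]:

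| Assumed ICC | Design effect | Effective n | Power |
|---|---|---|---|
| 0.01 | 1.15 | 451 | 89% |
| 0.04 | 1.60 | 324 | 77% |
| 0.05 | 1.75 | 297 | 73% |
| 0.10 | 2.50 | 208 | 58% |

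The article gives neither the ICC nor the mean class size, so these rows show a range, not an estimate.

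**The case against.** The best defence is that the cause cannot be proved. The design section describes a cluster trial and the analysis plans random intercepts, so the authors had clustering in mind. A journal article condenses, and an inflation of 1.65 might have been dropped in the editing. That possibility stands. Against it, the sentence attributes 580 to G-Power under a plain two-group design, and the coincidence with the 95% result is exact. On either reading the sentence needs correcting.

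It can also be said that 580 is literally sufficient, since it exceeds 352, so on its own terms the error is conservative. That is true for individually randomised students. It does not make 580 the output of the inputs printed beside it.

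Finally, this is a pilot. Its primary outcomes concern participation and feasibility, the between-group quantitative comparisons are secondary, enrolment is complete, and nowhere does the article compare 519 with 580. These points limit the consequences: no conduct or analysis changes. They do not bear on the arithmetic.

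**Conclusion.** The concern holds. With d = 0.3, alpha 0.05 and 80% power, a 1:1 two-group t-test needs 352 participants two-sided or 278 one-sided. The stated 580 is the exact two-sided total for 95% power and exceeds the 352 by 65%. This is a wrong stated figure, not an omitted detail, because the number and the inputs that fail to produce it appear in the same sentence.

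The conclusion assumes the standard independent-means calculation with 1:1 allocation, and 580 as a total across both arms. A misreported power setting is the most likely explanation but remains an inference. The 92.7% for 519 students must not be taken as evidence of adequate power for a class-randomised trial.

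**What to change.** Replace the sentence with one consistent pair, stating that the test is two-sided: either 352 in total for 80% power, or 580 in total for 95% power, each for d = 0.3 before clustering. Then state the assumed ICC and mean class size, and show the design effect applied to that total.

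If 580 already includes an inflation for clustering or dropout, say so and give the factor (1.65 relative to 352). If it is for clustering alone, give the ICC it rests on, about 0.04 at 16 students per class.

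The cost is a text correction. No data, recruitment or analysis changes. It should be made before results are reported under CONSORT, as section 2.6 commits to.

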## Discussion

3

Recent meta-analyses and systematic reviews provide growing evidence supporting physical activity breaks in schools, demonstrating benefits for students' physical activity levels (76–78), attention (79), academic performance (80, 81), health-related quality of life (82), and aerobic fitness (19, 83). These findings underscore the classroom as a promising setting for promoting physical activity with potential benefits for learning outcomes and student well-being. However, it is equally important to recognize that some reviews report modest or inconsistent effects, including weak trends or null findings, particularly regarding long-term impact, feasibility, and contextual variations in implementation success. These inconsistencies reveal critical knowledge gaps that necessitate further investigation into targeted, sustainable, and scalable approaches (11).

The MOVE12 study addresses these gaps through the evaluation of a systematically designed, classroom-based intervention developed using the robust, theory-driven Intervention Mapping (IM) protocol. By targeting both individual and environmental determinants, MOVE12 promotes short, student-led physical activity breaks (MOVE-breaks) integrated seamlessly into the school day. The intervention incorporates evidence-based components, peer-led sessions, autonomy-supportive structures, and minimal resource requirements, to enhance feasibility, adaptability, and sustainability across diverse school settings. Its multi-level approach considers individual, interpersonal, and organizational factors, ensuring comprehensive evaluation while addressing real-world challenges that affect intervention effectiveness.

Guided by the socio-ecological model (SEM) and self-determination theory (SDT), MOVE12 represents an innovative approach to integrating physical activity into upper secondary school routines. The IM protocol enabled a systematic and theory-informed process for designing, implementing, and evaluating this health promotion intervention. One of the key strengths of using IM lies in its step-by-step framework, which ensures each phase is grounded in theoretical and empirical evidence (30). This structure is particularly valuable for addressing complex health behaviors like physical activity, which are influenced by interdependent factors at multiple levels, from individual motivation to school culture and broader policies.

The MOVE12 study aims to build on previous efforts by embedding regular, short physical activity breaks throughout the school day. While prior interventions have shown varying levels of success, the strategy seeks to create an environment that actively supports sustained physical activity. By incorporating MOVE-breaks into daily school routines, the intervention has the potential to enhance adherence to physical activity guidelines (84, 85), achieving the recommended 60 min of moderate-to-vigorous physical activity per day (76, 86). Additionally, the flexible design allows schools to tailor the program to their specific contexts, effectively addressing variations in resources, constraints, and classroom structures across academic and vocational programs.

This study also enhances the theoretical understanding of intervention design by integrating SEM and SDT to create supportive environments that not only allow, but actively encourage regular physical activity among adolescents (35, 87). The intervention emphasizes autonomy and peer support, core SDT constructs that are shown to enhance motivation, engagement, and sustainability of behavior change. Research supports this dual approach, as interventions fostering autonomy, competence, and relatedness are more likely to be effective and maintained over time (38, 43).

Despite its strengths, the application of the IM protocol in MOVE12 poses several challenges. A significant issue is ensuring the fidelity across diverse school environments, particularly given structural differences between academic and vocational study programs in terms of classroom (88). Academic students typically work at desks in traditional classrooms, whereas vocational students experience more diverse working methods, such as alternating between standing and sitting, and varied classroom environments like workshops, specialized workspaces, and classrooms that differ according to the subject area. Variations in resources, commitment, and existing cultures among schools could affect the consistency and effectiveness of the intervention's implementation. This highlights the need for adaptable yet structured implementation strategies that can accommodate various school environments/contexts without compromising the intervention's integrity (89, 90). Another challenge is securing engagement from all stakeholders, particularly teachers who are not directly involved as teacher ambassadors (91, 92). Their broader involvement is crucial for the sustainable integration of physical activity interventions in schools, as they play a significant role in shaping school culture and student behaviors (93).

The MOVE12 study offers valuable insights for the design and implementation of health promotion interventions in educational settings. Future research should focus on the scalability of such interventions, exploring factors like school size, diverse demographics, and varying levels of existing infrastructure. From a policy perspective, MOVE12 has the potential to inform school-based strategies that address physical inactivity, contributing to improved public health outcomes. The evaluation of the MOVE12 pilot intervention will assess the effectiveness of the intervention mapping protocol in establishing a foundation for sustainable, scalable, and impactful physical activity interventions in schools.

